Several psychosocial interventions have been designed to reduce self-stigma and its impact on patient’s outcomes, with preliminary results on self-stigma, insight and self-efficacy [30]. Narrative enhancement and cognitive therapy (NECT) is a structured, 20 session group-based approach which combines psychoeducation to counteract SMI stereotypes, cognitive restructuring to challenge dysfunctional attitudes about the self and story-telling exercises to enhance meaning-making and the person’s ability to move beyond their illness-identity to a more integrated sense of self [31]. NECT is manualized and can be implemented with fidelity in routine treatment settings [31]. Four controlled studies, including three randomized controlled trials (RCT) in three different countries (USA, Israel, Sweden) have been published to date in psychotic-related disorders. NECT was effective in improving self-stigma, hope and self-esteem [32–34] with persisting effects after 6 months’ follow-up [33, 34]. The results on subjective quality of life were mixed, one study found improvements [32] but another found no effectiveness [33]. NECT was effective in reducing social withdrawal and avoidant coping strategies in participants with schizophrenia (SZ) in comparison with an active control condition [34]. However, NECT was not effective on social functioning, measured with the Quality of Life Scale [35], a global measure of psychosocial function [34]. In almost all studies of NECT, the samples were mixed, with some participants showing low levels of self-stigma (Internalized Stigma of Mental Illness (ISMI) total score < 2.5) and others moderate to high self-stigma (ISMI > 2.5). Changes in coping strategies were higher in participants from centres providing the intervention within the context of psychiatric rehabilitation [34].

In summary, NECT has demonstrated effectiveness on self-stigma and subjective aspects of recovery (hope, self-esteem and quality of life) in participants with psychotic-related disorders and SZ. Its effectiveness on social function and in other stigmatized SMI conditions (bipolar disorder (BD), borderline personality disorder (BPD)) are, however, still unclear. Similarly, NECT’s effectiveness in improving depression, treatment adherence, wellbeing and personal recovery is still unknown.

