#### Recruitment and randomization

Patients diagnosed with schizophrenia, bipolar disorder or borderline personality disorder (DSM-5 criteria [41]) will be recruited through six Rehabase psychiatric rehabilitation network centres [36], three FondaMental Academic Centres of Expertise (FACE) for SZ or BD [42, 43], one unit specialized in mood disorders at the Geneva university hospital, one psychiatric day-care clinic specialized in mood and personality disorders in Grenoble and one psychiatric rehabilitation centre located in the psychiatric hospital in Caen. The selected sites are already actively involved in treating patients with SZ, BD or BPD and have previous research experience in the field of psychiatric rehabilitation. Regular group meetings will be organized to monitor quality control and ensure good inter-rater reliability. A list of eligible participants will be generated under the supervision of the coordinating centre clinical research officer. Each eligible patient will be approached by a trained member of the research team and invited to participate in the study, thereby eliminating selection biases. Eligible patients will be given a leaflet describing the program and the research. Informed consent will be taken during a medical interview with one of the investigators. The clinical research officer of the coordinating centre (Grenoble) will be in charge of the randomization process for participants from all centres. Clusters will be randomized to receive the intervention at either T0 or T1. Stratified randomization will be used to ensure that cluster types are well balanced across groups. Outcomes will be compared in all groups at T0 and T1 (duration of intervention= 6 months). Six-month and 12-month outcomes for groups 1 and 2 will be measured at T2 (18 months after T0) to evaluate the stability of the effects over time. A 7-point improvement in social functioning measured using Personal and Social Performance Scale [44] (PSP) is generally considered as clinically significant. We plan to include 5 patients per centre and per group, meaning that there will be 10 participants included per centre for a total of 120 patients included (60 in group 1, 60 in group 2). This sample size was calculated using R package ‘pwr’ [45] based on Cohen [46] (*d* = 0.50, alpha level of 0.05) without allowing for intra-cluster correlations and the cluster and time effects found in stepped-wedge designs [47, 48]. This could be a considerable limitation, as it might have underpowered the trial [47]. Most of the outcome measures are self-rated questionnaires; the other evaluations will be conducted by an evaluator who has not taken part in the intervention. The schedule of enrolment, interventions and assessments is shown in Fig. 3 (SPIRIT diagram).

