### Assessments

At baseline and at follow-up, socio-demographic and illness-related information (education level, employment and marital status, psychiatric diagnosis, age of onset, illness duration, current pharmacological treatment) will be collected. All outcome measures listed below are part of routine clinical evaluations in the national REHABase and FACE networks for SZ and BD [36, 42, 43] approved by the relevant ethical committees.

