### Statistical analysis

Intention-to-treat analyses will be conducted in the first instance. The analyses will be conducted using parametric tests for normal distributed data (Student’s *t* and covariance analysis with repeat measures ANCOVA) and with non-parametric tests (Mann-Whitney *U* and Kruskal-Wallis test) in case of significant deviations from the normal distribution. The primary analysis was done by intention to treat.

We will analyse all outcomes using multilevel regression models with time point and intervention status as fixed effects and clusters as a random effect. Timepoint will be included as a categorical variable [39]. The statistical analysis will be done using the R software, version 3.2.3 [70]. The psych package version 1.5.8 will be used [71]. Effect size (Cohen’s *d*) will be calculated using the effsize package [71]. Size effects inferior to 0.20 will be considered as negligible, from 0.20 to 0.40 as small, from 0.40 to 0.60 as moderate and superior to 0.60 as strong [71]. The leaps package version 2.9 will be used for variable selection [72]. The level of confidence intervals will be set at 0.95 and the significance level of tests at 0.05.

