## Discussion and conclusion

NECT has shown effectiveness in reducing self-stigma in patients with psychotic-related disorders in a range of contexts in previous research. Considering the prevalence of moderate to high self-stigma in SMI and its impact on functional outcomes, NECT appears to be a promising intervention to complete the basket of services proposed by psychiatric rehabilitation centres (cognitive and social cognitive remediation, psychoeducation, social skills training, group cognitive behaviour therapy, vocational rehabilitation, peer-support [36]). If shown to be effective on social function and for different SMI, it is likely that NECT will have widespread implications for clinical practice.

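### The stated model gives one pooled NECT effect with no diagnosis term, so on its own it cannot show an effect in any one diagnosis; recorded diagnosis should be a pre-specified adjustment, with estimates by diagnosis

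*Protocol article*

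**What the plan says.** - **Model.** The Statistical analysis section gives one specification for all outcomes: "multilevel regression models with time point and intervention status as fixed effects and clusters as a random effect". Time point is categorical. No diagnosis term or intervention-by-diagnosis term is named. The section also mentions repeated-measures ANCOVA and a package for variable selection, without saying which variables.
- **Hypothesis.** The primary hypothesis at the end of the Introduction is a single comparison of NECT with control on social functioning.
- **Evidence gap.** The Introduction says of NECT: "Its effectiveness on social function and in other stigmatized SMI conditions (bipolar disorder (BD), borderline personality disorder (BPD)) are, however, still unclear".
- **Outlook.** The Discussion and conclusion reads: "If shown to be effective on social function and for different SMI, it is likely that NECT will have widespread implications for clinical practice".
- **Centres.** Under Recruitment and randomization, three centres are for schizophrenia or BD, one is a mood-disorder unit, and one is "one psychiatric day-care clinic specialized in mood and personality disorders in Grenoble". The other seven (six network centres and one rehabilitation centre in Caen) are not described by diagnosis. Centres are randomised, stratified by cluster type; the types are not defined.
- **Data.** The Assessments section lists "psychiatric diagnosis, age of onset, illness duration, current pharmacological treatment" among the items collected at baseline and follow-up.

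**The concern.** The article presents BD and BPD as open questions and links its practical implications to an effect across conditions, while the only effect it specifies averages over all of them. A positive pooled result need not apply to BD or BPD, and a null one could hide an effect there.

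Diagnosis also travels partly with the randomised unit. Moving a specialised centre from one group to the other moves about 10 patients of similar diagnosis together. If diagnoses differ in how PSP changes over six months, a chance excess of one diagnosis in a group enters the pooled contrast, and the stated model has no term to take it out.

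**Working it through.** **1. The plan's own figure.** The article plans "for a total of 120 patients included (60 in group 1, 60 in group 2"), from d = "0.50, alpha level of 0.05) without allowing for intra-cluster correlations". Power is not stated, so 120 cannot be reproduced exactly. Assuming two-sided testing and 80% power, n per group = 2 x (1.96 + 0.84)^2 / 0.50^2 = 62.8, so 63 per group and 126 in total (128 by the t-based calculation). At 60 per group, power is 0.78. The sample size is not disputed here; what matters is that it serves one pooled comparison.

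**2. What the pooled effect says about one diagnosis.** The diagnosis split is not given. Assume equal thirds: 40 per diagnosis, 20 per group, clustering ignored.
- 95% half-width for d within a diagnosis: 1.96 x sqrt(2/20) = 0.62 SD. With baseline adjustment at an assumed correlation of 0.6: 0.62 x sqrt(1 - 0.36) = 0.50 SD.
- Power for d = 0.50 within a diagnosis: Phi(0.50 / sqrt(2/20) - 1.96) = Phi(-0.38) = 0.35 (0.34 by t). It runs from 0.19 at 10 per group to 0.48 at 30 per group.
- Difference in effect between two diagnoses: SE = sqrt(4/20) = 0.447. Power for a 0.50 SD difference is 0.20; the difference detectable at 80% power is (1.96 + 0.84) x 0.447 = 1.25 SD.

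As an illustration, with equal thirds a pooled 0.50 fits effects of 0.50 in every diagnosis, and equally 0.75, 0.75 and 0, since (0.75 + 0.75 + 0)/3 = 0.50.

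**3. How far stratification balances the specialised centres.** Assume 6 centres per group.
- Without stratification there are 924 allocations, and the five specialised centres split 4:1 or 5:0 in 24% of them.
- With the six network centres split 3:3, the other six also split 3:3. One of those six is Caen, so the five specialised centres must split 3:2. This also holds if the three expert centres are a stratum of their own, split 2:1.

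**4. What the stated model passes on.** Expected bias was computed for the stated model with T0 and T1, 12 clusters of 10, and working intra-cluster correlation from 0.001 to 0.20.
- Differential 6-month change: a 3:2 split passes on 3/6 - 2/6 = 17%, whatever the correlation.
- Difference in level only: 5% to 16%, because T0 and the cluster effect absorb the rest.

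The 17% assumes that specialised centres hold only the diagnosis in question and the others none of it. If the surplus centre holds 100% and its counterpart one third, the shift is 10 x (1 - 1/3)/60 = 11 percentage points.

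**5. Size.** Assume diagnoses differ by 0.3 to 0.5 SD in 6-month PSP change (no figure is in the article).
- Low end: 0.11 x 0.3 = 0.03 SD. High end: 0.167 x 0.5 = 0.08 SD.
- Against d = 0.50: 0.033/0.50 = 7% to 0.083/0.50 = 17%.
- Against the standard error before clustering, sqrt(2/60) = 0.18 SD: less than half.

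**The case against.** The case on the other side is substantial.

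- **A condensed article.** Covariates and subgroup analyses are commonly left to a fuller document, and the Trial status section refers to protocol version 1.5, which is not shown. The variable-selection remark leaves room for covariates. A reader might infer that diagnosis is collected and then ignored; the documents do not establish that. What remains is that the article does state a model for all outcomes, and that unnamed, data-driven selection is not pre-specified adjustment.
- **No diagnosis-specific claim is planned.** The hypothesis is pooled, the Design section calls the study exploratory, and the closing sentence is conditional. A reader might infer that the trial intends to declare benefit in each condition; the text does not say so. Social function is itself named as a gap, and the Introduction reports that an earlier controlled study of NECT found no effect on it. A pooled PSP benefit would therefore be informative even if schizophrenia drove it. All this stands: the pooled test is legitimate for its hypothesis.
- **Randomisation is stratified.** This removes the 4:1 and 5:0 splits. It cannot divide three expert centres evenly or balance one-of-a-kind centres. The Geneva and Grenoble units fall in the same group in 33% to 40% of stratified allocations, and up to 33% of a difference in change would then pass through (0.10 to 0.17 SD on the same assumptions). A reader might take that as the expected bias. It requires both units to hold one diagnosis only and the other ten centres none of it, which the listed remits do not support: Grenoble covers mood and personality disorders, and the expert centres include BD.
- **By-diagnosis estimates will be imprecise.** True, and a reason to label them as estimation rather than to omit them.

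**Conclusion.** The point holds in limited form. The stated pooled model answers the pooled primary question but cannot on its own show an effect in any one diagnosis, although the article treats BD, BPD and breadth across conditions as part of what the trial informs.

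The imbalance issue is secondary: roughly 0.03 to 0.08 SD under a 3:2 split. It rests on an assumed 6:6 division of centres, strata set by centre type, and an assumed 0.3 to 0.5 SD diagnosis difference in change. It is chance imbalance in a single allocation. It does not support a reading that the primary comparison is systematically biased or invalid. The adjustment is worth making because diagnosis is already recorded and is partly tied to the randomised unit.

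**What to change.** 1. In the T0-T1 PSP model, add baseline diagnosis (schizophrenia spectrum, BD, BPD) and diagnosis-by-time point as pre-specified fixed effects, not left to variable selection.
2. Pre-specify one table of PSP effects by diagnosis with 95% confidence intervals, from an intervention-by-diagnosis model. Label it as estimation only, with no claim resting on its p-values.
3. Word the closing section so that a pooled result is claimed for the mixed population only.

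Cost: analysis text and one sentence, with no new data. Three diagnosis categories add 2 main-effect and 2 diagnosis-by-time parameters, so 4 in the main model; the by-diagnosis model adds 2 more. The diagnosis-specific intervals will be openly wide. The Trial status section says the trial has not started, so the change can still be made in advance.

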## Trial status

The present trial has not yet started. The recruitment will begin on September 1, 2019, with an estimated study completion date of April, 3, 2023. Protocol version 1.5 was written on April 2, 2019, and approved by the relevant ethical committee (CPP Nord-Ouest I) on April 26, 2019.

## Discussion and conclusion

NECT has shown effectiveness in reducing self-stigma in patients with psychotic-related disorders in a range of contexts in previous research. Considering the prevalence of moderate to high self-stigma in SMI and its impact on functional outcomes, NECT appears to be a promising intervention to complete the basket of services proposed by psychiatric rehabilitation centres (cognitive and social cognitive remediation, psychoeducation, social skills training, group cognitive behaviour therapy, vocational rehabilitation, peer-support [36]). If shown to be effective on social function and for different SMI, it is likely that NECT will have widespread implications for clinical practice.

## Data Availability

The study protocol is available online on Clinical Trials: https://clinicaltrials.gov/ct2/show/NCT03972735?term=nect&rank=1
